**PARTICIPANT NUMBERS & POWER**

Using G*Power, it was determined that 52 participants would be needed to detect a large, post-treatment, between-group effect size with alpha set to 0.05 and 80% power (Faul et al., 2007). This is because previous meta-analyses have detected large effect sizes for the effect of CBT on anxiety (Cuijpers et al., 2013). Previous preliminary randomised control trials of CBT for LGBTQ+ adults with both internalising and externalising disorders have recruited samples of similar sizes (Pachankis et al., 2015; Pachankis et al., 2020).

Power was also calculated to detect clinically meaningful changes in participant anxiety disorder diagnosis according to DSM criteria. Using the ClinCalc LLC (2024) sample size calculation tool, the recruitment of 42 participants would be sufficient to detect a post-treatment between-group clinically meaningful change in anxiety disorder diagnosis with 80% power and alpha set to 0.05. This is based on the anticipated incidence of anxiety remission drawn from the metanalysis of Springer et al. (2018), which found that 55.8% of anxiety disorder diagnoses remitted after receiving CBT. For waitlist controls, anxiety disorder symptoms in participants in waitlist control fell below the clinical cut-score 15.4% of the time (Scott et al., 2022). Given CBT has not been examined in trials of LGBTQ+ participants with only internalising disorders (Van Der Pol-Harney & McAloon, 2018), an exact power analysis is unable to be determined and is thus an exploratory estimate. However, 95% confidence intervals will be reported with any effect estimates to determine the intervention's precision.

A total of 16 – 20 participants will be selected for inclusion in the qualitative study, with eight to ten participants each from groups one and two (after receiving treatment). Braun and Clarke (2013) recommend that 10 to 20 participants are typically sufficient to identify themes, although, suggested that fewer participants may be needed if the sample holds more information power (Malterud et al., 2016). This is because four of the five aspects of the information power model suggested by Malterud et al. (2016) indicate higher information power and, thus, a smaller sample size in this study. This is indicated by the narrow aim of the qualitative study (to understand the feasibility and acceptability of telehealth-adapted CBT in LGBTQ+ participants), the specificity of the population (LGBTQ+ participants with diagnosed depressive or anxiety disorders who have received remotely-delivered CBT), the use of CBT and minority stress theory, and strong dialogue potential given the interviewer will have researched the subject area and will be using an interview guide. This sample size is consistent with other sample sizes in this area of research (Jackson et al., 2022; Pachankis et al., 2020). Participants will be selected based on a representative matrix to achieve a maximally diverse qualitative sample, consistent with other qualitative studies (Christensen et al., 2023). A lack of characterisation of diverse groups has been an issue in previous studies (Hall et al., 2019)

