| **Statistical considerations** | **Sample size calculation**  The sample size calculator developed by Faul et al. (2007) was used to calculate a total sample size of 52 participants, in samples of 26 for each group, to detect a large effect (*d* = .80) with 80% power. Previous research has indicated that CBT has a large effect size for anxiety disorders (Cuijpers et al., 2013). To detect clinically significant differences in participant diagnostic status, 42 participants will need to be recruited, in samples of 21 in each group, using the ClinCalc LLC (2024) sample size calculation tool.  A total of 16 – 20 participants will be selected for inclusion to the qualitative study, with eight to ten participants each from each intervention group. Braun and Clarke (2013) recommend that 10 to 20 participants are typically sufficient to identify themes, although, previous researchers have suggested that fewer participants may be needed if the sample holds more information power. This sample size is consistent with other sample sizes in this area of research (Jackson et al., 2022; Pachankis et al., 2020). Participants will be selected based on a representative matrix to achieve a maximally diverse qualitative sample, consistent with other qualitative studies (Christensen et al., 2023).  **Analysis plan**  To ensure analyses manage missing data conservatively, intent-to-treat principles and mixed-linear models will be used for quantitative analyses. Mixed-models are used to analyse longitudinal clinical trial data robustly. Using an appropriate covariance structure and maximum likelihood estimation will provide unbiased estimates in the event of missing data, assuming that data is missing at random. Qualitative data will be analysed using framework analysis (Ritchie & Spencer, 1994). |
| **Study duration** | 5 years |

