- **Recruitment.** Given preliminary power estimates, should at least 52 participants be recruited, then the recruitment methods for CBT delivered via video-conferencing for anxiety disorders will be judged to be feasible. Given power estimates to find clinically meaningful differences in anxiety outcomes, should at least 42 participants be recruited, then the recruitment methods used in this trial may have preliminary feasibility for CBT delivered via video-conferencing for LGBTQ+ adults with anxiety disorders.
- **Questionnaire Completion**. Given power estimates and previous drop out-rates, should sufficient participants complete questionnaires to complete adequately powered analyses, the chosen psychometrics may be suggested to be feasible to be completed via telehealth for LGBTQ+ adults with anxiety and depressive disorders.
- **Treatment Fidelity.** Clinician fidelity to the treatment manuals, as assessed by a supervising clinical psychologist based on treatment manual checklists, will also be assessed. Borrelli et al. (2005) recommended that 80% adherence to treatment guidelines might be assessed as ‘high treatment fidelity’. Supervising clinicians will code fidelity to the treatment manual for 10% of sessions.

All self-report data will be collected via REDCAP. The questionnaire administration schedule is outlined in Table 1 below. Participants in the control group will be re-assessed with the pre-treatment measures and diagnostic interview prior to starting treatment.

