**ANALYSIS PLAN**

To meet the study’s aim (i.e., to understand if the treatment is efficacious for reducing symptoms of anxiety disorders ), the following analyses will be conducted. The main analyses looking at treatment outcomes from the RCT will be carried out using conservative intention-to-treat principles and using mixed-linear models analyses to handle missing data. Mixed-models are a robust statistical approach for analysing longitudinal clinical trial data and these analyses will employ an appropriate covariance structure and maximum likelihood estimation, which provides unbiased estimates in the case of missing data, under the assumption that data is missing at random. These analyses account for the effect of missing data, thus additional participant recruitment to account for drop-out rates is not warranted. Using this dataset, other appropriate analyses arising from secondary papers will also be conducted. Participants have been informed in the PICF that other secondary data analyses will be conducted on the data that they provide during their participation in the research trial. This may include intersectional moderator analyses of treatment efficacy based on person-level stigma moderators from the minority stress model to inform further treatment adaption needs (Barrera & Castro, 2006; Meyer, 2003). Comparisons between the standard treatment and the LGBTQ-affirmative CBT protocol will be compared using benchmarking analyses (Minami et al., 2008).

To understand the treatment’s efficacy, clinically significant change will be measured using three methods. Diagnostic change will be assessed from pre- to post-treatment and at follow-up using the DIAMOND structured interview. Treatment response will be measured using the reliable change index (RCI) of Jacobson and Truax (1991) to understand which change on the OASIS is not attributable to measurement error, but rather is statistically reliable. Any increase in symptoms by the RCI magnitude of change will be defined as deterioration in this trial. Clinically significant change at post-treatment and to follow-up will be defined as a score below the cut score of 8 on the OASIS (Campbell-Sills et al., 2009).

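### The 80% power claimed for diagnostic status at 42 participants combines two different outcomes and allows for no lost interviews, so it is not supported

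*Protocol*

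**What the plan says.** Under Participant Numbers & Power, the protocol gives a second calculation besides the one for the primary symptom outcome: "Power was also calculated to detect clinically meaningful changes in participant anxiety disorder diagnosis according to DSM criteria". The target is "clinically meaningful change in anxiety disorder diagnosis with 80% power and alpha set to 0.05". Two rates feed it. For CBT, a cited meta-analysis found that "55.8% of anxiety disorder diagnoses remitted after receiving CBT". For the waitlist, a second meta-analysis found that "anxiety disorder symptoms in participants in waitlist control fell below the clinical cut-score 15.4% of the time". The Summary gives the result: "42 participants will need to be recruited, in samples of 21 in each group".

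The Analysis Plan says that mixed linear models account for missing data, "thus additional participant recruitment to account for drop-out rates is not warranted". It also lists diagnostic change on the DIAMOND interview and an OASIS score below 8 as two separate ways of measuring clinically significant change.

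The Participant Retention item under Secondary Measures cites 15.9% drop-out before CBT starts and 26.4% during it, and accepts about 80% retention after the waitlist and 70% after treatment. The Recruitment item that follows reuses the smaller sample size, with reference to the power estimate: "should at least 42 participants be recruited, then the recruitment methods used in this trial may have preliminary feasibility".

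**The concern.** A comparison of two proportions needs the same event in both arms. Here one arm contributes remitted diagnoses and the other contributes symptoms falling below a cut-score. The Analysis Plan keeps these two kinds of outcome apart. No waitlist rate of diagnostic remission appears anywhere, and 15.4% is not labelled as a stand-in for one.

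Separately, 42 is described as the number to recruit but is the number that must be analysed. The stated reason for making no allowance does not carry over to diagnostic status. Under missing at random, a linear mixed model protects against bias; it does not put back the information lost with a missed interview. It is also a model for a continuous score, not for a binary diagnosis.

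At stake are a stated power and a feasibility tier justified by it. Recruitment that stopped at 42 could be reported as preliminarily feasible on the strength of a power that the protocol's own retention figures do not deliver.

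**Working it through.** **Inputs.** p1 = 0.558, p2 = 0.154, alpha 0.05, power 80%, 21 per arm (Summary; Participant Numbers & Power). Planned size is 26 per arm. Loss figures are 15.9% and 26.4% (cited drop-out) and 20% and 30% (complements of the accepted retention). Sidedness and test are not stated.

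**Reproducing 42.** Two-sided, pooled, without continuity correction:

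n = [1.960·√(2p̄(1−p̄)) + 0.842·√(p1(1−p1) + p2(1−p2))]² / (p1−p2)², with p̄ = 0.356

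= [1.327 + 0.517]² / 0.404² = 3.400 / 0.1632 = 20.8, so 21 per arm and 42 in total.

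The figure is reproduced, with no room for loss. Power at 21 per arm is 80.3% by the normal approximation and 82% by exact enumeration of the uncorrected chi-square test.

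**Effect of lost interviews**, with both rates unchanged. Normal approximation:

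Power = Φ{[|p1−p2| − 1.960·√(p̄(1−p̄)(1/n1+1/n2))] / √(p1(1−p1)/n1 + p2(1−p2)/n2)}

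| Loss | Evaluable per arm from 42 | Power | Evaluable per arm from 52 | Power |
|---|---|---|---|---|
| 0% | 21.0 | 80.3% | 26.0 | 88.4% |
| 15.9% | 17.7 | 72.7% | 21.9 | 82.0% |
| 20% | 16.8 | 70.4% | 20.8 | 79.9% |
| 26.4% | 15.5 | 66.5% | 19.1 | 76.3% |
| 30% | 14.7 | 64.1% | 18.2 | 74.1% |
| 26.4% CBT, 15.9% waitlist | 15.5 and 17.7 | 70.0% | 19.1 and 21.9 | 79.4% |
| 30% CBT, 20% waitlist | 14.7 and 16.8 | 67.7% | 18.2 and 20.8 | 77.3% |

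Exact enumeration of the uncorrected chi-square test for the cited arm-specific loss needs whole numbers. From 42 recruits it gives 69% at 15 v 18 and 76% at 16 v 18. From 52 it gives 84% at 19 v 22, against 90% at 26 v 26 with no loss. The gap between 15 v 18 and 16 v 18 is mostly discreteness, so ranges are safer than single values.

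**Effect of the waitlist rate.** The documents give no diagnostic remission rate for the waitlist, so this is an assumed range. CBT is held at 55.8%, with no loss:

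| Assumed waitlist remission | Power at 21 v 21, approximation | Power at 21 v 21, exact chi-square | Needed per arm |
|---|---|---|---|
| 10% | 91.5% | 93% | 16 |
| 15.4% | 80.3% | 82% | 21 |
| 20% | 67.9% | 69% | 28 |
| 25% | 53.1% | 54% | 39 |

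**Sensitivity to the test.** Fisher's exact test has 70% power at 21 v 21 and 83% at 26 v 26. The continuity-corrected formula gives 26 per arm. These are context only, since the protocol names no test.

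**The case against.** The strongest reply is that 42 is a side calculation. Enrolment is fixed at 52, driven by the primary symptom outcome, and at 52 the diagnostic comparison has about 90% power with no loss. The protocol also calls its power analysis exploratory, promises 95% confidence intervals, and describes a feasibility trial. The 42 tier is worded softly, sits below a main criterion of 52, and triggers no stopping or analysis rule. All of that stands and limits the consequence. The exploratory caveat does not dispose of the point, though: its stated reason is the lack of trials in this population, not mixed outcomes or missing interviews.

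The drop-out figures are also rates of leaving CBT, not of missing a DIAMOND interview. People who stop therapy may still be interviewed, and the 15.9% concerns people who never start CBT, so applying it to the waitlist arm is a scenario. This stands too, and the loss results are conditional on it. The protocol gives no expected interview completion to use instead.

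A reader might infer three stronger things that the documents do not support. First, that 42 was miscalculated: it was not; a standard formula returns it. Second, that the mixed outcomes make 80% too high: a waitlist remission rate below 15.4% would make it too low, and how far the two events differ cannot be judged without the cited sources. Third, that true power is 70% because an exact test is needed: no test is named, and that choice may properly sit in the statistical analysis plan.

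**Conclusion.** The concern holds in a limited form. The arithmetic of 42 is sound; the 80% attached to it is not supported. On the outcome mismatch, the size and direction of the error are unknown: power at 21 v 21 runs from 93% to 54% over an assumed waitlist remission of 10% to 25%. On loss, the direction is certain and the size conditional. If interview loss falls in the 15.9% to 30% range taken from the protocol's own figures, 42 recruits give about 64% to 76% power with an uncorrected test.

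This does not show that the planned trial is too small. At 52, power for diagnostic status is about 74% to 84% at 20% to 30% loss or the cited arm-specific loss, depending on method, if 55.8% and 15.4% are accepted. The primary OASIS calculation is a separate matter. The practical weakness is the stated power and its reuse to justify the 42 tier; correcting both is worthwhile and cheap.

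**What to change.** - **Summary (Statistical considerations) and Participant Numbers & Power:** use one definition of diagnostic remission for both arms. Failing that, label 15.4% a proxy and show power over a range on both sides of it, such as 10% to 25%. State the power for the expected number of DIAMOND completers at the planned 52.
- **Analysis Plan:** limit the statement that no drop-out allowance is warranted so that it does not cover diagnostic status.
- **Recruitment item under Secondary Measures:** remove the 42-participant tier, or keep it without describing it as the size powered for clinically meaningful differences.

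The cost is wording only. No participants are added and no procedure changes. The stated power for diagnostic status will look less favourable.

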**PARTICIPANT RECRUITMENT**

Recruitment of participants will use a variety of methods. Flyers will be placed across University of Technology Sydney campus and other community noticeboards (Appendix A), on social media platforms like Facebook, LinkedIn, and Instagram (Appendix B), on Twitter (Appendix C), on professional networking sites for psychologists (Appendix D) and sent via email or letter to health professionals in Australia such as general practitioners, psychologists, counsellors, social workers, and psychiatrists (Appendix E). The student investigator may also directly approach health professionals and health services by phone, email, or in person to inform them of the study and provide the approved recruitment flyer. Health professionals or services that serve LGBTQ+ clients will be prioritised for contact. Social media posts will be made on the research team’s professional social media accounts. The moderators of relevant social media sites will be approached to advise of the potential for clients to access support through the study. Agreement will be obtained from at least one moderator before posting any approved script. Paid Google Advertisements may be posted (Appendix F) periodically. Applications to relevant not-for-profit organisations (Appendix G) will be made to advertise the study via their website and social media pages, including One Door Mental Health (<https://www.onedoor.org.au/resources/referral-forms/external-research-study-application-form>) and SANE Australia (<https://www.sane.org/adrc/external-research-projects>).

Participants for the qualitative nested study will be selected from the treatment sample using a representative matrix. This will ensure a broad representation of different participants perspectives and will be based on scores of the post-treatment Client Satisfaction Questionnaire (CSQ), sexual orientations, gender identities, racial and ethnic diversity, geographically located participants, and degree of completion of treatment.

All participants will be advised that as part of the study, they may be invited to a qualitative interview to understand their experience and preferences during the treatment. This will be included in the initial PICF form, and participants will be given the option to change their mind or decline participation in the qualitative interview with no impact on their relationship with their assigned clinician or the research team. Participants who completed at least one treatment session would be invited to attend the qualitative interview after completing their second structured diagnostic interview. An email will be sent to all participants selected to attend prior to their second diagnostic interview, which is attached in Appendix H. Should a participant be selected on the basis of the representative matrix, and decline, then the next participant with demographic characteristics in the representative matrix that has not yet included in the qualitative study will be selected to participate in the qualitative study.

**STUDY PROCEDURES**

Prior to engaging with the study, potential participants can read about it via the recruitment methods described above, or on the UTS-affiliated website for the study and related studies by participants (<https://www.uts.edu.au/about/graduate-school-health/clinical-psychology/what-we-do/clinical-psychology-research/telepsych-laboratory>).

All recruitment methods will include a link for participants to access and consent to the PICF. After consenting to the PICF, participants will proceed through the study in the procedure outlined below and in Figure 1:

**1. Online Screening**

Participants will follow a REDCAP link to read the online PICF. Participants who consent will then complete the demographic form, the DIAMOND screener, and the PHQ-9 to assess suitability. This is anticipated to take 20 – 30 minutes. Participants will provide their name and contact details (phone number and email address) for an interviewing clinician to contact them to complete the videoconferencing delivered diagnostic interview. Participants will be asked to indicate their preferred times for diagnostic screening.

Participants who do not meet the criteria for the study will be shown a screen providing information on how to access support and crisis services. Non-eligible participants will be informed if it is likely they meet the criteria for one of the disorders and will be encouraged to seek support from appropriate services such as their GP (Appendix I).

**2. Diagnostic Screening**

Based on the online screening questionnaires, participants who meet all the study criteria will be invited to a diagnostic interview using the DIAMOND (Appendix J). The purpose of the interview is to confirm their diagnostic status and assess comorbid conditions. Participants will be asked to confirm their email address and preferences for treatment on a particular day or time. Diagnostic interviews will be conducted via videoconferencing and will be audio-recorded. Once diagnostic criteria are confirmed, these participants will be randomised to a treatment condition. Diagnostic screening is anticipated to take 1 – 2 hours but may be longer for some participants.

If a participant does not meet the study criteria at this stage, they will be informed by one of the research staff via email (Appendix K) after the student clinician and chief investigator have confirmed they do not meet criteria via discussion. Then, an investigator will contact the participant to discuss treatment options. These participants will be encouraged to access support from their GP or appropriate services, including crisis services if necessary.

**3. Randomisation**

If a participant meets all the study criteria, then they will be randomised to either an immediate treatment group or a waitlist control group (WLC). Randomisation will be conducted using a random number generator via the website www.random.org to ensure unbiased selection. Assessing clinicians will not be aware of the randomisation status of participants and will be advised of their participants’ group randomisation by the Principal Investigator. Participants will be advised of their group assignment, along with their acceptance into the study, via email. An email with a REDCAP link to pre-treatment questionnaires will be sent to participants in both groups to be completed. After the competition of these questionnaires, participants in group 1 (immediate treatment) will be called to schedule treatment to begin as soon as possible. Participants in group 2 (waitlist control) will be called 9 weeks later to complete the diagnostic interview and self-report questionnaires and schedule treatment as soon as possible.

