**Summary**

| **Overall project title:** | Remote Cognitive Behavioural Therapy for LGBTQ+ People with Anxiety Disorders: An Exploratory Trial |
| --- | --- |
| **Protocol version** | 2.3 |
| **Objectives** | **Primary**  The primary objective of this program of research is to understand how efficacious cognitive behavioural therapy (CBT) is when delivered via videoconferencing for anxiety disorders in LGBTQ+ adults.  **Secondary**  The secondary objectives of this project are: 1) to benchmark the efficacy of adapted CBT compared to standard CBT for LGBTQ+ adults, when both are delivered via video-conferencing; 2) to understand the feasibility of delivering CBT to LGBTQ+ adults via video-conferencing; and 3) understand the perspectives of LGBTQ+ participants on the content, delivery format, and acceptability of CBT delivered via telehealth for anxiety disorders. |
| **Study design** | A randomized controlled trial (RCT) compliant with CONSORT-R guidelines, comparing an immediate treatment group with a waitlist control group, with a nested qualitative study to examine acceptability of the treatment. |
| **Planned sample size** | A total sample of 52 participants, with 26 participants in each group. Qualitative interviews will use 8 - 10 participants from each intervention group, with a total of 16 - 20 included participants in qualitative evaluation interviews. |

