It is noted by the researchers that most people presenting for treatment with an internalising disorder have experienced their symptoms for several years (Patton et al., 2014). This means that participants have likely consulted multiple medical or mental health clinicians without complete or partial remission of symptoms. Minority stressors for LGBTQ+ participants are also by nature managed by LGBTQ+ people chronically in the long-term (Meyer, 2003), and thus unlikely to need urgent care within the eight-week period of the waitlist, while receiving treatment for eight weeks, or during follow-up. In any case, this study is not a crisis service, and participants who need urgent care will be referred out at assessment to seek urgent psychiatric care or support from their primary care provider.

Management of risk will be ongoing throughout the project. Importantly, all participants will be made aware of what steps they can follow in a mental health emergency in multiple communication modes at multiple timepoints. For example, which services to contact and what to do in a mental health crisis is outlined in (1) the PICF; (2) a safety plan provided to all clients at the beginning of treatment; (3) in every email communication with participants. Secondly, participants' responses to their questionnaires will be monitored, meaning that deteriorating or consistently elevated symptoms will trigger the research team to contact the participant to encourage contact with their health care team or emergency services. All communication between participants and the research team will be documented.

Assessed for eligibility.

Participants who do not meet criteria will be excluded.

Three-month follow-up diagnostic assessment.

Post-treatment diagnostic assessment and self-report questionnaires.

Qualitative Interviews (n = 10)

Allocated to immediate intervention with Unified Protocol (n = 26).

Post-treatment diagnostic assessment and self-report questionnaires.

Qualitative Interviews (n = 10)

Three-month follow-up diagnostic assessment.

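### The randomisation section names a website number generator but nothing that secures the stated 26:26 split or guards the draw, and it tells participants their group before the baseline OASIS

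*Protocol*

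**What the plan says.** The Protocol commits to equal arms in several places. The Summary plans "A total sample of 52 participants, with 26 participants in each group". The group definitions under Objectives, Design, and Hypotheses repeat 26 for each group, and so does Figure 1, for example "Allocated to immediate intervention with Unified Protocol (n = 26").

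The method is stated once, under Study Procedures, section 3 (Randomisation): "Randomisation will be conducted using a random number generator via the website www.random.org to ensure unbiased selection". Section 2 (Diagnostic Screening) places this step after each participant's diagnostic criteria have been confirmed.

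The only sentence that touches on masking is also in section 3: "Assessing clinicians will not be aware of the randomisation status of participants and will be advised of their" participants' group by the Principal Investigator.

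Section 3 then describes, in this order: an email telling participants that they are accepted and which group they are in; an email to both groups with the link to the pre-treatment questionnaires; and, once these are complete, a call to the immediate-treatment group to schedule sessions. Table 1 shows the OASIS first collected at Week 0, with no entry in the screening column.

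**The concern.** Three things are missing from a section that sets out to fix the allocation method.

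- **Restriction.** Nothing links a number generator to two arms of exactly 26. There is no blocking, no list prepared in advance and no rule mapping numbers to groups.
- **Protection of the draw.** No one is named as generating or holding the sequence, and no record of each draw is required. A draw could be repeated, or an enrolment reconsidered, once the result is seen, and nothing stated would prevent or reveal this. The claim of unbiased selection covers only how the number is produced.
- **Order of allocation and baseline.** Participants who already know whether they will wait can be the ones filling in the baseline OASIS.

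The stakes come from the design. Participants and therapists know the treatment, the primary outcome is self-reported, and some eligibility items rest on judgement (suicide risk and cognitive impairment at interview). A baseline influenced by knowledge of the group would feed directly into every change from baseline. These are matters of trial conduct that belong in a protocol, not details usually left to an analysis plan.

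**Working it through.** **Inputs.** Total 52, 26 per group (Summary; Figure 1). Effect size and power: "to detect a large effect (*d* = .80) with 80% power" (Summary). Alpha 0.05 (Participant Numbers & Power). The test is assumed two-sided, because the Protocol does not say.

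**1. Reproduce the plan's sample size.** For a two-sample t-test with arms n1 and n2, df = n1 + n2 − 2 and the noncentrality is d × √(n1·n2/(n1 + n2)).

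- 26:26: 0.80 × √(676/52) = 0.80 × √13 = 2.88, df 50, power 80.7%.
- 25 per arm gives 79.1%.

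So 26 per arm is the smallest number reaching 80%, and the stated 52 is reproduced. The one-sided version (20 per arm by the normal approximation) does not match.

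**2. Split if each participant gets an independent 1:1 draw (assumption).** The size of one arm is Binomial(52, 0.5).

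- P(exactly 26:26) = C(52,26)/2^52 = 0.110.
- The central 95% range for one arm is 19 to 33. The expected difference between arms is 5.7.

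| Split | P(this or worse) | Power at d = 0.80 |
| --- | --- | --- |
| 26:26 | – | 80.7% |
| 30:22 | 33.2% | 79.8% |
| 32:20 | 12.6% | 78.6% |
| 34:18 | 3.6% | 76.8% |

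At 32:20 the noncentrality is 0.80 × √(640/52) = 2.81. Averaged over all splits, power is 80.0%, a loss of about 0.8 points.

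**3. Split if draws are independent until one arm reaches 26 (alternative assumption).** This forces 26:26, but every later allocation is then known. The expected number of such forced allocations is 52 × C(52,26)/2^52 = 52 × 0.110 ≈ 5.7 participants.

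**4. Split with a blocked list.** With 13 blocks of 4 (an assumed size), 13 × 2 = 26 per arm exactly, and power is 80.7%. With varying sizes, the same holds if the blocks sum to 52.

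**5. Order of allocation and baseline.** No arithmetic applies. Section 1 (Online Screening) lists the demographic form, the DIAMOND screener and the PHQ-9, and Table 1 has no OASIS at screening. Section 3 gives notification of group first and the pre-treatment questionnaires next. On the stated order, no OASIS score is taken before the group is known.

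**The case against.** A reader might infer that the allocation is unconcealed and cannot deliver 26:26. The Protocol does not support that.

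- **The split.** The text does not say that draws are independent or made one at a time. The same website could be used to build a balanced list beforehand. The binomial figures are therefore conditional, and the supportable statement is that 26:26 is not secured. The 26 per group is also labelled a planned size, mixed models do not need equal arms, and 8 to 10 interviewees can still be found in an arm of 20. All of this stands, and the cost of imbalance is minor.
- **Concealment.** A number drawn only after eligibility is settled cannot be foreseen by the enrolling clinician. Foreknowledge, the usual concealment threat, is absent on that reading. This stands too. What remains is a redraw or a reversal of enrolment, which the text neither describes nor guards against. Much of eligibility rests on structured measures, and exclusion after interview needs agreement between the student clinician and the chief investigator. That narrows the opportunity without closing it.
- **The assessor sentence.** It can be read in time order: unaware while assessing, told afterwards. That is a reasonable reading, but the sentence gives no timing. It describes assessor masking more than protection of the draw.
- **Baseline order.** Step 1 of the Summary's study procedures mentions baseline questionnaires during screening, which could suggest a pre-allocation baseline. The detailed sections and Table 1 do not place the OASIS there.
- **REDCap.** The Protocol uses it for consent, screening and questionnaires. It says nothing about a randomisation function, so REDCap can only be suggested as a vehicle.

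**Conclusion.** The point holds as a gap in specification plus a stated sequence that should be changed. The Protocol fixes 26 per group and names a number generator, but it gives no restriction, no independent holder and no record of the draw. If the draws are simple 1:1, the stated split occurs in only 11.0% of trials, and 32:20 or worse occurs in 12.6%. The loss of power is about 2 points at 32:20 (80.7% − 78.6% = 2.1) and 0.8 points on average, so power is not the reason to act.

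The reason is exposure to selection bias in an open trial, together with a self-reported primary outcome whose baseline can be completed with the group already known. The size of either bias cannot be estimated from the Protocol, and nothing in it shows that a draw would in fact be repeated. This is a worthwhile, low-cost improvement and does not undermine the design.

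**What to change.** In section 3 (Randomisation), replace the sentence on the number generator with wording to this effect: a 1:1 permuted-block list with randomly varying block sizes is generated before enrolment and held by a team member who neither assesses nor treats participants. It is kept in REDCap if a randomisation function is available there, and otherwise in any protected list. Each allocation is logged, and is released only after eligibility is confirmed and the Week 0 questionnaires are complete.

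Reorder the rest of the section to match, so that the email stating the group follows the Week 0 questionnaires. Bring step 1 of the Summary's study procedures into line. Reword the assessor sentence to say at what point assessors are told the allocation.

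**Cost.** The sample size stays at 52 and no visits are added. There is some set-up work. People who do not return the Week 0 questionnaires would not be allocated, so reminders may be needed. Blocking brings slight predictability in an open trial; varying the block sizes, and not disclosing them to those who enrol, reduces this but does not remove it.
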